## Abstract

**Background:**

Depression in older adults deteriorates quality of life and increases morbidity, mortality, and medical expenses. Medicine and social policy should work together to decrease this burden. Existing prevention studies are often based on time-consuming psychotherapies, which therefore are not feasible for a wide application at the community level. Postcard interventions have been shown to be effective for patients after hospitalization for major depression, drug overdose, or self-harm. This paper describes the protocol of a pragmatic, randomized controlled trial designed to examine the efficacy of a postcard intervention for depression among community-dwelling individuals aged 65 years or older.

**Methods/Design:**

This is a pragmatic, non-blinded, parallel comparison, randomized controlled trial using Zelen’s design in a community setting. Participants will include community-dwelling older adults (aged 65 years or older) with limited social support (indicated by eating meals alone) and with symptoms of depression (scoring 4 or higher on the 15-item Geriatric Depression Scale (GDS)). The intervention will consist of sending postcards with handwritten messages and seasonal reports from a historical city to participants once a month for eight consecutive months. Self-addressed, stamped envelopes will be enclosed to facilitate non-obligatory replies. Primary outcomes will be changes in the GDS scores that are administered to all elderly inhabitants of the community every year as part of annual health checks. Secondary outcomes include quality of life as measured by a visual analogue scale, and self-rated basic and advanced activities of daily living. We will also examine the subjective sense of effectiveness of the intervention, recollection of the number of intervention mailings received, and the number of mailed replies as the index of the acceptability of the postcard intervention. The time × group interaction for two consecutive years will be analyzed using a generalized linear mixed model. To detect an effect size of 0.5 at alpha error of 0.05 and statistical power of 0.80, 63 participants per group are required. Based on an estimated consent and dropout rate of 70%, a total of 180 subjects will be recruited.

**Trial registration:**

UMIN000010529

## Background

Depression is frequent and chronic in older adults. According to research on community-dwelling older adults, the proportion of individuals reporting depressive symptoms is 2.8% to 35% [1]. The natural course of later-life depressive disorders is poor: a 6-year follow-up study showed that 76% of patients followed an unfavorable but fluctuating course or a severe chronic course of depression, and only 23% of patients experienced full remission [2].

Depression in older adults deteriorates the sufferers’ quality of life (QOL) more than many other chronic diseases [3]. It gives a negative impact on patients’ QOL in various ways, including wellbeing, perceived physical functioning, bodily pain, and general health perceptions [4]. The mortality rate of people with depression was found to be 1.8 times larger than that of non-depressed subjects due to suicide, unhealthy habits, and medical illnesses [5].

Depression is also costly. Depressed older adults use more outpatient resources than those without depression, including frequent appointments and increased laboratory and radiographic tests. They also have more non-specific medical complaints, and this is associated with increased total ambulatory care costs [6]. A study in the United States found that the additional medical cost per one depressed older adult was USD 686 for 1 year and USD 5,271 for 4 years [7].

As the world population continues to age, there is an urgent need therefore for medicine and social policy to find ways to reduce and prevent depression in older adults in the community.

However, to the best of the authors’ knowledge, no simple, effective interventions currently exist for the prevention of depression in the elderly population [8]. The existing prevention studies have limitations in study design or rely on time-consuming psychotherapy, which is unrealistic for a community prevention program. They need weekly sessions with a duration of 45 to 120 minutes for 6 to 10 weeks [9-12], and trained workers or specialists [9,11-14]. The subjects of most of the studies were not general people in community but those with specific disease or physical symptoms such as diabetes [10], macular degeneration [11], hip fracture [15], chronic pain [12], and most of the studies recruited subjects in clinical settings [10,11,13,15]. Some studies lacks sample size calculation [9,10,12] and were quasi-randomized controlled trials [10,14].

A postcard intervention was first carried out in the United States in 1976 for suicide prevention among discharged major depression patients. Researchers sent 24 letters over 5 years and reported that this significantly decreased suicide rates for the first 2 years and tended to lower suicide rates up to 13 years in total [16,17]. Three more postcard intervention trials were conducted in Israel and Australia in 2005, 2010, and 2011, that focused on the prevention of drug overdose or self-harm. The results showed significant decrease in the number of drug overdose episodes, and the rates of suicide ideation and suicide attempts [18-21]. The prevention of depression in patients with a recent stroke by postcard is also planned [22].

The advantage of the postcard intervention is its low personal and financial cost: it only requires paper, pencil, and postage. Therapists are not required to visit the participants and vice versa. If the postcards do not contain medical and related information, a wide range of people such as elementary school students can take part in the intervention program.

This paper describes the study protocol for a pragmatic, randomized controlled trial designed to examine the effectiveness of the postcard intervention for improvement of depression in community-dwelling individuals aged 65 years or older. This study will focus in particular on those who have increased depressive symptoms and insufficient social support at baseline, because it is expected that the intervention is more effective among such individuals.

### Objectives

For community-dwelling older adults (aged 65+ years) reporting symptoms of depression and limited social support, this study aims to: (1) examine the effectiveness of a postcard intervention for the improvement of depressive symptoms; (2) evaluate the effectiveness of a postcard intervention in global geriatric health indicators such as quality of life (QOL) and the activities of daily living (ADL); and (3) assess the acceptability of the postcard intervention.

## Methods and design

### Ethical approval

The Institutional Review Board (IRB) of the Graduate School of Medicine, Kyoto University has reviewed and approved the study protocol and informed consent documents (E1658, 12 February 2013).

### Study setting

The study will be conducted in the community of a rural town, located in the center of Shikoku, one of the four main islands in Japan. Its main industries are agriculture and forestry. It has a population of 4,407, of whom 1,711 (38.8%) are aged 65 years or older.

Our study team has been conducting a longitudinal observational study in this community since 2004, in which we administer comprehensive geriatric assessments and report results and make referral to physicians as necessary. This observational study has been approved by the IRB of the Graduate School of Medicine, Kyoto University (E-18), and written informed consent has been obtained from all the participants.

### Study design

#### Design overview

We will conduct a pragmatic, non-blinded, parallel comparison, randomized controlled trial using Zelen’s design in this community. Figure 1 depicts the participants’ flow. Participants will be selected based on the questionnaire surveys including a self-rated depression scale. Participants will then be randomized to the intervention or no-intervention groups at a 1:1 ratio using computer-generated random numbers. Randomization will be stratified by gender and self-rated depression scale score. To conceal group assignments, random number generation and group allocation will be conducted at the same time by an independent epidemiologist not involved in the participant recruitment or intervention or assessments. Informed consent forms will be mailed to those assigned to the intervention group. Postcards will be sent to the consenting participants once a month for eight consecutive months. They will be enclosed with a self-addressed stamped envelope to facilitate non-obligatory replies by mail. As this is a pragmatic study, any treatment outside the trial will be permitted. Self-reported outcomes will be measured at baseline and post intervention; the questionnaire about participants’ impression of effectiveness of the intervention and their recollection of the number of postcards received will be measured after treatment.

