#### Zelen’s design

The study uses a randomized controlled trial with the single consent version (Zelen’s design) [23,24]. This is a variation of the standard randomized controlled design in which participants are randomized to intervention or control before consent is sought. Consent is obtained from the intervention group only after the randomization. The most important advantage of this method is that participants know the intervention they will receive at the time of consent. In a conventional randomization, participants who agree to join the study may retract their consent or continue participation with reluctance after finding out their assigned intervention, whereas the Zelen’s method requires a decision only on the allocated intervention.

The main ethical concern is that consent is obtained only from the intervention group. To overcome this point, the revised Zelen method has been proposed [25]. This method is a combination of an observational study and a randomized controlled trial. Eligible participants first consent to an observational study, and then they are randomly assigned to intervention and control groups; those in the intervention group are asked to consent to participate in the study. Those in the control arm are not informed of this, but will be followed in the observational study if they agreed. Our protocol will follow this method.

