### Participants

#### Inclusion criteria

Participants will meet the following criteria: (1) being 65 years of age or older; (2) exhibiting symptoms of depression with a score of ≥4 on the self-rated 15-item Geriatric Depression Scale (GDS-15); and (3) reporting that they eat meals alone in the questionnaire.

The study will include individuals with sub-threshold depression. Indicated prevention aimed at sub-threshold depression is said to be most efficient in terms of costs and benefit [26]. As there are no agreed-upon definitions of sub-threshold depression on GDS-15, the study will include those with scores ≥4 points on the GDS-15, which is 1 point below the established cutoff to detect major depression [27].

Considering the nature of the intervention, the study will target those who are at risk of social isolation. We hypothesize that eating alone, rather than living alone, better represents the risk of isolation. In fact, eating alone was more strongly associated with depression than living alone among community-dwelling older adults [28].

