### Sample size

To detect an effect size of 0.5 with *P* = 0.05 at 80% power, 63 participants are required per group. Assuming a non-consent and dropout rate of 30%, a total of 180 subjects are needed. Based on the results of our previous observational study performed in the same town in 2012, this sample size is believed to be feasible.

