## Discussion

The study protocol describes the design of a pragmatic randomized controlled trial to verify the efficacy of postcard intervention to prevent and improve depression among community-dwelling older adults in Japan. This is the first application of the postcard intervention for depression of community-dwelling older adults. The advantage of the postcard intervention is its low human and financial cost, which cannot be matched by other existing approaches such as psychotherapy. This intervention can be carried out by anyone who can write a letter. Its application will be broad.

There are three advantages to the study. First, the study is set in the community, whereas previous postcard interventions were conducted in clinical settings [16-19,21]. Considering the potential of postcard interventions, however, application to a broader field is desirable; the application in community settings targeting local residents is but one of them. Second, the study focuses on people who eat alone, not those who live alone. The supposed effect of postcard intervention is to make a connection with people, thereby reducing feelings of isolation. Even if a person is surrounded by many other people, he or she will be lonely unless people pay attention to him or her. In this sense, eating alone rather than living alone can reflect true isolation [28]. Third, the study will evaluate ADLs. Previous prevention studies did not consider their effect on ADLs. However, as the participants in this study are older adults whose ADLs have bidirectional interactions with depressive mood, the influence of ADLs should be considered and the effects of the intervention on AADL in particular should be evaluated.

If the efficacy of the postcard intervention for depression in community-dwelling older adults is verified, it will be a milestone in community intervention.

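### Individuals are randomised although people who eat alone but live with others are eligible, so two eligible co-residents can be split between arms, which may expose the control member to the letters and may reveal the trial

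*Protocol article*

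**What the plan says.** Under Design overview the unit of allocation is the person: "Participants will then be randomized to the intervention or no-intervention groups at a 1:1 ratio using computer-generated random numbers". The only strata are the two named there: "Randomization will be stratified by gender and self-rated depression scale score". Household plays no part.

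The isolation criterion is "reporting that they eat meals alone in the questionnaire". Inclusion criteria gives the reason: "We hypothesize that eating alone, rather than living alone, better represents the risk of isolation". The Discussion confirms that people living among others belong to the target group: "Even if a person is surrounded by many other people, he or she will be lonely unless people pay attention to him or her". Exclusion criteria removes only people who cannot understand and sign the consent form and those living in a hospital or institution. There is no one-per-home rule.

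On the control arm, the section on Zelen's design says: "Those in the control arm are not informed of this, but will be followed in the observational study if they agreed". It adds that the trial will follow this method. Consent forms are posted to the intervention arm only, and those who consent then receive eight monthly letters, each with a reply card (Design overview; Intervention).

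**The concern.** Selecting on eating alone brings in people who share a home. Two of them, such as a couple or a parent and an older child who eat separately, can both be 65 or older and both score 4 or more on the GDS-15. With individual allocation, one may be in the intervention arm and the other a control.

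Two things could then go wrong.

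- **Dilution.** The control member may read or share the letters, which pulls the GDS-15 difference towards zero.
- **Disclosure.** The consent form or the letters may tell the control member that a trial is running. The trial is not blinded and the primary outcome is self-rated, so this knowledge may change the answers. The direction cannot be predicted. Disclosure would also run against the stated procedure for controls, even if no letter were ever shared.

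**Working it through.** **1. Inputs.** The Abstract states: "To detect an effect size of 0.5 at alpha error of 0.05 and statistical power of 0.80, 63 participants per group are required". The Sample size section adds: "Assuming a non-consent and dropout rate of 30%, a total of 180 subjects are needed". The article gives no count of homes with two or more eligible people, so that share is an assumption below.

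**2. The plan's own figure.** By the normal approximation, two-sided, n per group = 2(1.960 + 0.842)² / 0.5² = 62.8, rounded up to 63. Then 126 / 0.70 = 180. Both stated figures reproduce. The exact t-test power at 63 per group is 0.795, or 0.801 by the normal approximation. The t-test value is the baseline below.

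**3. Chance that a pair is split.** With independent 1:1 allocation, the two members land in different arms with probability 0.5. If the arms were forced to exactly 90 and 90, it would be 90/179 = 0.503. Taking 0.5, the chance of at least one split among m eligible pairs is 1 − 0.5^m:

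| Eligible pairs (assumed) | Chance of at least one split | Expected splits |
|---|---|---|
| 1 | 50% | 0.5 |
| 2 | 75% | 1 |
| 5 | 97% | 2.5 |
| 10 | 99.9% | 5 |

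**4. Share of controls affected.** Let s be the share of the 180 participants who are in such pairs. There are 180s/2 pairs, half of them split, and each split pair contributes one control. The affected share of the 90 controls is (180s/4)/90 = s/2.

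**5. Upper bound on the power loss.** Suppose every affected control receives the whole effect. The diluted effect is then 0.5 × (1 − s/2).

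| s (assumed) | Controls affected | Effect | Power, 63 per group |
|---|---|---|---|
| 0 | 0% | 0.500 | 0.795 |
| 5% | 2.5% | 0.4875 | 0.775 |
| 10% | 5% | 0.475 | 0.753 |
| 20% | 10% | 0.450 | 0.707 |

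**6. More realistic cases.** Letters go only to people who consent. If the whole 30% allowance were non-consent, 70% of split pairs would receive letters. The exposed shares become 1.75%, 3.5% and 7%, the effects 0.491, 0.4825 and 0.465, and power 0.781, 0.766 and 0.736. If instead all consent but controls receive half the effect, power is 0.785, 0.775 and 0.753.

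**7. Cost of keeping co-residents together.** The design effect is about 1 + s × ICC. With s = 10% and ICC 0.3 (both assumed), it is 1.03. That gives 65 per group and 186 in total. Full sharing at the same s would need 70 per group and 200 in total to restore 80% power. To first order, contamination inflates the required n by 1 + s × f, where f is the fraction of the effect that reaches the control. Splitting thus costs more than clustering whenever f exceeds the ICC, and of the two only splitting biases the estimate.

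**The case against.** The case on the other side is substantial.

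- **Exposure is not certain.** Letters are sealed, go only to consenters, and partly answer the recipient's own messages. This stands. A reader might infer that a split necessarily exposes the control member and reveals the trial, but the article supports only that it may. The privacy argument is itself partial: the handwritten part depends on the participant having replied, which is optional, and the rest is printed seasonal news that is easily passed round.
- **The design was not chosen to keep controls unaware.** A reader might infer that split homes defeat the purpose of Zelen's design. The article gives a different main advantage, namely that people know their allocated intervention when they consent. Leaving controls uninformed is a stated procedure, not the stated rationale.
- **Such pairs are probably rare.** Two people at one address must both eat alone, both be 65 or older and both score 4 or more. This stands as a judgement, although the criteria may cluster within a home and the article gives no count.
- **Dilution is conservative.** It moves the result towards no difference and does not by itself create a false positive. This stands for dilution. The effect of disclosure on self-rating has no known direction.
- **Stratifying by gender does not worsen matters.** Any independently allocated pair is split about half the time, whatever the sexes of its members.
- **The article is condensed.** A rule for shared addresses might sit in a fuller document. However, the article does fix the unit of allocation and the strata, and household is in neither.

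**Conclusion.** The point holds in a limited form. As written, the plan can place two eligible co-residents in different arms, with about an even chance per pair, and can send a consent form and letters to a control's own address. That sits badly with the procedure of not informing controls.

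The size is unknown and probably small. Power of 71% to 78% is an upper bound that rests on an assumed 5% to 20% of participants in such pairs, full consent and full transfer of the effect. If nearly all addresses hold one participant, the low end applies and the loss is about two points or less. The stated 63 per group and 180 in total are not in error.

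The reason to act is that the problem is foreseeable, that a larger sample would not remove dilution or disclosure bias, and that prevention is cheap.

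**What to change.** In Design overview, add one rule to the allocation. Before randomising, the independent epidemiologist identifies eligible people who share an address and allocates them together to one arm, with the stratum set by the first-listed member. All single-participant addresses stay individually randomised within the gender and GDS strata.

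In Statistical analysis, add a household term to the mixed model or use household-robust standard errors. Report the number of addresses with two or more participants.

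The cost is a few clusters of two, slightly less exact stratum balance, and a loss of precision that is negligible if such addresses are few. If there are none, the rule changes nothing. It does not address contact between participants from different homes in the same town.

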**Figure 1 F1:**
[figure not shown]
**Participant flowchart.** GDS-15: 15-item Geriatric Depression Scale; AADL: activities of daily living; BADL: basic activities of daily living; QOL: quality of life.

#### Zelen’s design

The study uses a randomized controlled trial with the single consent version (Zelen’s design) [23,24]. This is a variation of the standard randomized controlled design in which participants are randomized to intervention or control before consent is sought. Consent is obtained from the intervention group only after the randomization. The most important advantage of this method is that participants know the intervention they will receive at the time of consent. In a conventional randomization, participants who agree to join the study may retract their consent or continue participation with reluctance after finding out their assigned intervention, whereas the Zelen’s method requires a decision only on the allocated intervention.

The main ethical concern is that consent is obtained only from the intervention group. To overcome this point, the revised Zelen method has been proposed [25]. This method is a combination of an observational study and a randomized controlled trial. Eligible participants first consent to an observational study, and then they are randomly assigned to intervention and control groups; those in the intervention group are asked to consent to participate in the study. Those in the control arm are not informed of this, but will be followed in the observational study if they agreed. Our protocol will follow this method.

